### Control group

All activities will be provided by professionally trained recreational therapists who have been specifically informed about the study.

In the control group, recreational day activities will be offered under exactly the same circumstances as the music therapy sessions: a total of 16 weekly sessions, each lasting 45 min, every week at exactly the same time as the music therapy intervention. As in the intervention group, a treatment guide specifies the treatment procedures for the control group. In this guide, the setting and general goals are outlined. The main goal of the recreational activities is to enhance communication skills by way of encouraging and stimulating the patients in interaction.

The activities vary from reading the newspaper, cooking, arts-and-crafts/handwork or puzzles/games. Musical activities, such as singing along or watching a music-video are not allowed, nor will background-music be played. The recreational therapist is well instructed about and fully aware of this restriction. Besides that, during the whole study, participants from the control group are not allowed to receive music therapy. Both the physician who is responsible for the referrals and the music therapists are fully aware of this limitation. Participation in in regular musical activities however (such as watching a music video or attending a music-performance which takes place on the ward occasionally) is allowed. These activities are not considered to be music therapy and are open to all patients that reside in the institution, regardless of participation in the study. Also, listening to music in the privacy of their own room is allowed for all participants.

All participants are allowed to leave the session at all times.

The music therapy and the recreational day activities will be provided in separate rooms, away from the ward. Participants will be taken to the music therapy room or the activity room by the nursing staff. The music therapist and the recreational therapist make sure that they can start the moment all participants are in the room. After the session, the participants will be taken back to the ward by the nursing staff. The therapists will never leave a participant in the room unattended.

After each session, a short report of the activities will be written by both therapists, including an evaluation of each patient. Since a self-report from the patient himself is not feasible, the reports written by the therapists will be used for evaluation purposes and treatment fidelity.

### Compliance with treatment

In each participating center a monitor will be identified, to be responsible for adherence to study protocol (including data collection).

Furthermore, after each session, both therapists will document significant events, notable behaviors, and interventions applied. These reports will enable us to determine whether the treatment has been conducted as intended. These reports will provide insight into the patient’s state of mind at the time of the intervention. This information can help us explain why certain measurements might be significantly different compared to others in the same patient. Self-reports (the patients’ own perception) might not be feasible, due to the rapid decline of cognitive skills (see rationale), Furthermore, this information will also be used to evaluate the process of the study.

### Outcome measures

The primary outcome measure, communication skills, will be assessed by the social-cognitive domain of the Behaviour Observation Scale Huntington (BOSH) [26]. The secondary outcome measure, behavior, will be assessed by both the Problem Behaviours Assessment-short version [27, 28] and the third domain (mental rigidity and aggression) of the BOSH (mental rigidity and aggression).

The BOSH contains 32 items in 3 subscales: 1) activities of daily living (ADL) (5 items), 2) social-cognitive functioning (15 items), and 3) mental rigidity and aggression (12 items). Each item is assessed on a 4-point scale. The scores from the first subscale (ADL) range from 1 (self-supporting) to 4 (nursing required). The sum score from the first scale may range from 5 to 20. The scores from the second subscale (social-cognitive functioning) range from 1 (unaffected) to 4 (contact no longer possible); the sum score may range from 15 to 60. Finally, the scores from the third subscale (mental rigidity and aggression) range from 1 (never) to 4 (always); the sum score may range from 12 to 48. Intra- and interrater reliabilities are respectively 0.83 and 0.95 [26].

Assessment of the BOSH will take place within a week before the first intervention (baseline assessment), and will be repeated within a week after the 8th and again within a week after the 16th intervention. 12 weeks after the last intervention, the BOSH will be repeated.

The BOSH takes 15 min and will be administered by nursing staff in charge of the daily care of the patients. Blinding the BOSH-assessors might not be feasible as the nursing staff will have to transport the patients to and from the therapy-rooms. Also in daily life, the chance of the patient divulging his or her allocation towards the nursing staff is big. However, in the process-evaluation following the study all the assessors will be asked whether they were aware of the allocation of the patients.

Since the BOSH is a commonly known assessment scale in the participating HD nursing homes in The Netherlands, no formal training will be carried out prior to the start of the study unless the particular nursing home has no experience with the BOSH.

Behavioral problems will be assessed with the Problem Behaviours Assessment-short (PBA-s) version [27, 28]. This is a 5-point rating scale, using the scores 0 (absent) to 4 (severe). The PBA-s is a 11-item semi-structured interview and assesses behavioural problems in the 4 weeks prior to the interview. The sum score may range from 0 to 40. In addition, there is a subscale for severity and one for frequency. The PBA-s is a validated and reliable measurement-tool: the interrater reliability is 0.74 for severity and 0.76 for frequency scores (mean kappa), and 0.94 for severity and 0.92 for frequency scores (weighted kappa) [29]. The respondents of this face to face semi-structured interview are the patient and a knowledgeable informant (spouse or caregiver) together.

Assessment of the PBA-s will take place following the same time-schedule as the BOSH-assessments. The PBA-s will be scored by independent, formerly trained assessors who will be blinded to group allocation of the patients. After the last assessment, the assessor will be asked whether or not he inadvertently found out about the patient’s allocation in order to verify the success of the blinding. Where possible, subjects are interviewed in the presence of a knowledgeable informant (primary caregiver).

After consulting a member of the PBA-workgroup we decided to adjust the 4-week retrospective view of the PBA-s to 1 week, due to the short time-frame in which it is administered (every 8 weeks).

### Sample size

The minimal clinically important change or difference (MCIC/MCID) in the scale serves as important input for the sample size calculations. Unfortunately, data about these scale-characteristics are unavailable. We anticipate that the population in the present study will differ little from the population previously used in the study by Timman et al. [26] from which we derived data on means and standard deviations for the subscales of the BOSH. If we assume that the values in the control group will change little over the course of the study, whereas those in the experimental group will improve by 25 %, and if we further assume an α of 0.05 and a β of 0.20, then the following sample size would be required:ADL: original mean ± SD = 2.25 ± 0.88; improvement of 25 % will result in a mean of 1.69 and if we conservatively estimate a reduction in SD to 0.75, we would require an N of 30 per group for the ADL subscale (for an effect size of 0.55 (moderate));Social-Cognitive: original mean ± SD = 2.10 ± 0.79; improvement of 25 % will result in a mean of 1.58 and if we conservatively estimate a reduction in SD to 0.75, we would also require an N of 30 per group for this subscale (for an effect size of 0.52 (moderate)).

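### The assumed 25% improvement is taken on item means whose lowest value is 1, so it amounts to 45–48% of all possible improvement and understates the size of the assumed effect

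*Protocol article*

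**What the plan says.** All references are to the protocol article.

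- **Outcome measures.** The social-cognitive items "range from 1 (unaffected) to 4 (contact no longer possible"), with 15 items and a sum of 15 to 60. The ADL items also run from 1 (best) to 4 (worst), with 5 items and a sum of 5 to 20.
- **Sample size, target.** The section reports that no data on a minimal important change or difference exist. It then assumes that "those in the experimental group will improve by" 25%. Its assumption for the comparison arm is that "the values in the control group will change little over the course of the study".
- **Sample size, ADL.** "original mean ± SD = 2.25 ± 0.88"; the improvement "will result in a mean of 1.69", with the SD reduced to 0.75 and 30 per group required.
- **Sample size, social-cognitive.** "original mean ± SD = 2.10 ± 0.79"; the improvement gives 1.58, again with SD 0.75, and "we would also require an N of 30 per group for this subscale".
- **Sample size, error rates.** "if we further assume an α of 0.05 and a β of 0.20". Whether the test is one- or two-sided is not said.

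**The concern.** A percentage change has a fixed meaning only on a scale with a true zero. Here the best possible item score is 1, so a mean of 2.10 contains 1 point that no treatment can remove and 1.10 points of measurable impairment. Taking 25% of the whole 2.10 removes much more than a quarter of the impairment. Coding the same items 0 to 3 would leave every patient and every SD unchanged, yet the same 25% would then describe a much smaller target.

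This matters because the percentage is the only reason given for the size of the target. A reader may well take the trial to be planned around a reduction of impairment by one quarter, and may later take a non-significant result as evidence against a benefit of that size. The social-cognitive subscale is affected, and the Outcome measures section names it as the primary outcome.

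**Working it through.** **Inputs.** From Sample size: means 2.25 and 2.10, SDs 0.88 and 0.79, reduced SD 0.75, α 0.05, power 0.80, 30 per group. From Outcome measures: item floor 1, sums 5–20 and 15–60. Allocation is 1:1 (Randomisation).

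**Step 1: what kind of means these are.** 2.25 and 2.10 lie below the lowest possible sums (5 and 15), so they cannot be sum scores. They fit item means on the 1–4 coding. This is an inference; the section does not say so.

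**Step 2: the plan's own figures.**
- ADL: 0.25 × 2.25 = 0.5625, and 2.25 − 0.5625 = 1.69. This agrees with the text.
- Social-cognitive: 0.25 × 2.10 = 0.525, and 2.10 − 0.525 = 1.58. This agrees.
- n per group, two-sample t-test, two-sided 0.05, 80% power, SD 0.75, with the printed (rounded) means: ADL difference 0.56 gives 30, as stated. Social-cognitive difference 0.52 gives 34, not 30.
- Power at 30 per arm for social-cognitive: d = 0.525/0.75 = 0.70, power 76% (75% with the rounded 0.52).
- A one-sided test with the unreduced SDs gives 32 (ADL) and 30 (social-cognitive), so one-sided testing could come close to 30 for both.

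**Step 3: share of the possible improvement.** Share = 0.25 × mean / (mean − 1).
- ADL: 0.5625 / 1.25 = 45%.
- Social-cognitive: 0.525 / 1.10 = 48%.
- On the social-cognitive sum: 15 × 0.525 = 7.9 of 15 × 1.10 = 16.5 points.

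**Step 4: 25% of the room above the floor** (the same as 25% on 0–3 coding).
- ADL: 0.25 × 1.25 = 0.3125. Social-cognitive: 0.25 × 1.10 = 0.275.

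Unadjusted t-test, two-sided 0.05:

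| Subscale | Difference | SD | Power at 30 per arm | n per arm for 80% |
|---|---|---|---|---|
| ADL | 0.3125 | 0.75 | 35% | 92 |
| ADL | 0.3125 | 0.88 | 27% | 126 |
| Social-cognitive | 0.275 | 0.75 | 29% | 118 |
| Social-cognitive | 0.275 | 0.79 | 26% | 131 |

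**Step 5: allowing for baseline adjustment.** The Statistical analysis section plans a repeated-measures mixed model that takes baseline into account. The documents give no baseline–outcome correlation r, so a range is assumed. As a simple approximation, residual SD = 0.75 × √(1 − r²), with 30 per arm:

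| Assumed r | Residual SD | Power, social-cognitive 0.275 | Power, ADL 0.3125 |
|---|---|---|---|
| 0.5 | 0.650 | 36% | 45% |
| 0.7 | 0.536 | 50% | 60% |
| 0.8 | 0.450 | 64% | 75% |

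**Step 6: smallest difference that would be significant.** Unadjusted, SD 0.75, 58 degrees of freedom: 2.00 × 0.75 × √(2/30) = 0.39. For social-cognitive that is 0.39/1.10 = 35% of the room.

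**The case against.** The strongest reply is that the target is fully defined. The section prints the start mean, the end mean and the SD, so anyone can subtract and obtain the absolute difference. Neither that difference nor the SD changes under recoding, the article fixes the coding at 1–4, and with no minimal important difference available any percentage is a convention. Most of this stands. There is no arithmetic error in the 25% step, and the sample size does not depend on coding once the means and SD are given. The figure of 118 per arm answers a different question, namely a smaller target. What the reply does not rescue is the percentage itself, which is the only justification offered and has no coding-free meaning.

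Two stronger readings are tempting, and the documents do not support them.

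- A reader might infer that the trial can detect nothing smaller than removal of about half of the impairment. That confuses the planning target with the smallest significant difference: an observed social-cognitive difference of about 0.39, or 35% of the room, already reaches significance without adjustment.
- A reader might infer that a true one-quarter reduction would usually be missed. That holds for the unadjusted test, but the planned model uses baseline. At r = 0.7 power for social-cognitive is about even, and at r = 0.8 it is 64%.

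Nor does the article say outright that the trial can detect a moderate 25% improvement. Its wording is conditional, and the label moderate is attached to the effect sizes of 0.55 and 0.52, not to the percentage.

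**Conclusion.** The point holds as one about how the target is expressed and justified. The assumed effect is 45% (ADL) and 48% (social-cognitive) of all improvement the subscales can show, not a quarter of the impairment. For a one-quarter reduction of impairment, power at 30 per arm stays below 80% in every case examined: 26–29% and 27–35% unadjusted, and 36–64% and 45–75% with baseline adjustment at SD 0.75 and r from 0.5 to 0.8. Separately, under a two-sided unadjusted test with SD 0.75, the social-cognitive target itself has about 76% power, not 80%.

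The conclusion rests on two assumptions: that 2.25 and 2.10 are item means, and that the source study used the 1–4 coding given in the article. The adjusted power figures also rest on the assumed correlations and on a single-time-point approximation to the mixed model.

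**What to change.** Keep N=60 and revise the sample-size paragraph:

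1. Say that the means are item means on the 1–4 coding, if that is confirmed, and state the target as an absolute difference: 0.56 item-mean points for ADL, and 0.525 for social-cognitive, which is about 7.9 points on the 15–60 sum.
2. Say that these are 45% and 48% of the improvement available above the floor, and do not describe the trial as powered for a one-quarter reduction of impairment.
3. Add the power at 30 per arm for 25% of the room above the floor, unadjusted and over a stated range of baseline–outcome correlations.
4. State whether the test is one- or two-sided. If two-sided, report about 76% unadjusted power for the social-cognitive target with SD 0.75.

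The cost is a rewritten paragraph. No patients are added and neither design nor analysis changes, but the stated sensitivity of the trial becomes less favourable.

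### The sample-size paragraph labels raw mean differences as moderate effect sizes, and for the primary subscale its inputs give about 73-74% power at 30 per group in an unadjusted two-sided test, not 80%

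*Protocol article*

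**What the plan says.** The Outcome measures section names the primary outcome: "The primary outcome measure, communication skills, will be assessed by the social-cognitive domain of the Behaviour Observation Scale Huntington (BOSH". The Sample size section takes means and SDs for two BOSH subscales from an earlier study of the scale. It assumes little change in controls and a 25% improvement under music therapy, with "an α of 0.05 and a β of 0.20".

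- **Social-cognitive:** the starting point is "Social-Cognitive: original mean ± SD = 2.10 ± 0.79". The mean is to fall to 1.58 with an SD of 0.75, and the result is that "we would also require an N of 30 per group for this subscale (for an effect size of 0.52 (moderate".
- **ADL:** 2.25 with SD 0.88 is to fall to 1.69. The text continues "if we conservatively estimate a reduction in SD to 0.75, we would require an N of 30 per group for the ADL subscale", with an effect size given as 0.55 and also called moderate.

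The paragraph does not say whether the test is one- or two-sided, and it uses no baseline correlation. The Study design section randomises sixty patients, which is 2 x 30. The Statistical analysis section plans a repeated-measures mixed model that takes baseline differences into account.

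**The concern.** An effect size described as moderate is normally read as a standardised difference, that is, a mean difference divided by an SD. Here the printed value equals the difference itself for social-cognitive and almost equals it for ADL. A reader who puts 0.52 into a two-group formula gets roughly twice the stated N. A reader who standardises with the printed SDs gets a larger effect, but still not 30 per group under a conventional two-sided test.

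The paragraph therefore cannot be reproduced as it stands, and its 80% power for the primary outcome is not supported by its stated inputs without a further assumption. A non-significant result would be read against that 80%.

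**Working it through.** **Inputs (Sample size section).** Social-cognitive 2.10 (SD 0.79) against 1.58 (SD 0.75). ADL 2.25 (SD 0.88) against 1.69 (SD 0.75). Alpha 0.05, beta 0.20, 30 per group. Allocation is 1:1 (Randomisation section). Sidedness is not given, so both are shown.

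**Step 1. The printed effect sizes.**
- Social-cognitive: 2.10 - 1.58 = 0.52, exactly the printed value.
- ADL: 2.25 - 1.69 = 0.56; printed 0.55.

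Neither has been divided by an SD.

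**Step 2. Can they be standardised effects at N = 30?** The normal approximation is n per group = 2(z_alpha + z_beta)^2 / d^2.
- d = 0.52, two-sided: 2(1.960 + 0.842)^2 / 0.52^2 = 15.70 / 0.2704 = 58.1, so 59. The t-test gives 59.03, so 60.
- d = 0.52, one-sided: t-test 46.4, so 47.
- d = 0.55: t-test 52.9, so 53 two-sided; 41.6, so 42 one-sided.
- Power at 30 per group with d = 0.52 is 51% two-sided and 64% one-sided.

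So the printed effect size and the printed N do not fit together in a two-group test of either sidedness.

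**Step 3. Standardise with the paragraph's SDs.**
- Social-cognitive pooled SD = sqrt((0.79^2 + 0.75^2)/2) = sqrt(0.5933) = 0.770; d = 0.52/0.770 = 0.675 (0.682 with the unrounded 25% difference of 0.525).
- ADL pooled SD = sqrt((0.88^2 + 0.75^2)/2) = 0.818; d = 0.56/0.818 = 0.685 (0.688 with 0.5625).

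**Step 4. Required N and power at 30 per group.** Unadjusted two-sample t-test, alpha 0.05. Ranges cover the rounded and unrounded differences.

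| Subscale, SD used | d | n per group, two-sided | Power at 30, two-sided | n per group, one-sided | Power at 30, one-sided |
|---|---|---|---|---|---|
| Social-cognitive, 0.79 in both arms | 0.66-0.67 | 37-38 | 71-72% | 29-30 | 81-82% |
| Social-cognitive, 0.79/0.75 | 0.68 | 35-36 | 73-74% | 28 | 83% |
| Social-cognitive, 0.75 in both arms | 0.69-0.70 | 34 | 75-76% | 26-27 | 84-85% |
| ADL, 0.88 in both arms | 0.64 | 40 | 68% | 31-32 | 79% |
| ADL, 0.88/0.75 | 0.69 | 35 | 74-75% | 27-28 | 84% |
| ADL, 0.75 in both arms | 0.75 | 29-30 | 81% | 23 | 89% |

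The normal approximation gives up to one patient per group fewer and about one percentage point more power. For the 0.79/0.75 case it is 0.675 x sqrt(30/2) - 1.960 = 0.655, a power of 74.4%. Simulated t-tests with SDs 0.79 and 0.75 gave 73.1%.

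**Step 5. Where 30 can be reproduced.** Two-sided, it appears for ADL with SD 0.75 in both arms, but the same method gives 34 for social-cognitive. One-sided with the observed SDs, the requirement is 29-30 and 31-32, within two patients of 30 for both subscales. The article does not say which route was used.

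**Step 6. Baseline adjustment (correlation r assumed).** Adjustment multiplies the SD by sqrt(1 - r^2). With 30 per group, two-sided, SDs 0.79/0.75 and the normal approximation, power is 78% at r = 0.3 and 86% at r = 0.5. In the t-test, 30 per group needs d = 0.736 for 80%, so r = sqrt(1 - (0.675/0.736)^2), about 0.40. The normal approximation gives about 0.36.

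**The case against.** The strongest reply is that the power shortfall is not shown for the trial as planned. Three parts of it stand.

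- **Sidedness.** The paragraph says only "if we further assume an α of 0.05" and does not call the test two-sided. One-sided, 30 per group is enough for social-cognitive under every SD choice. Two-sided is the usual reading and no one-sided test is declared, but the shortfall has to be stated as conditional on it.
- **Analysis.** The planned model takes baseline into account, and a moderate baseline correlation would restore 80%. No correlation is given, so this can be neither claimed nor ruled out.
- **Direction of the mislabel.** The printed 0.52 is smaller than the standardised 0.68. The label understates the assumed effect and is not what causes the shortfall.

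Three stronger readings are tempting, and the document does not support them.

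- **That calling the SD of 0.75 conservative is an error.** The word can describe the size of the reduction. If the SD shrank in proportion to the mean, it would be 0.75 x 0.79 = 0.59 and 0.75 x 0.88 = 0.66, so 0.75 is a modest reduction by comparison.
- **That controls will improve and remove the contrast.** The control guide does say "The main goal of the recreational activities is to enhance communication skills by way of encouraging and stimulating the patients in interaction", and the sample-size assumption is "If we assume that the values in the control group will change little over the course of the study". But a stated goal is not evidence of improvement, little change is not the same as none, and any figure for control improvement would be invented.
- **That attrition lowers power further.** The article gives no loss rate, and a condensed article may leave that to the full protocol.

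None of this rescues the effect-size label, which is incompatible with 30 per group whichever sidedness is chosen.

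**Conclusion.** The labelling error is certain: 0.52 is a raw difference, 0.55 is a slightly misprinted raw difference of 0.56, and neither is a standardised effect compatible with 30 per group in a two-group comparison. The standardised effects implied by the stated SDs are about 0.68 and 0.69.

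The power shortfall for the primary subscale is real but conditional. It holds for an unadjusted two-sided 0.05 test with the stated means and SDs, under every choice among those SDs: about 35-36 per group are needed (34-38), and 30 give about 73-74% (71-76%).

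A reader might infer that the trial simply lacks 80% power. The document does not establish that, given the unstated sidedness and the planned baseline adjustment. What it does establish is that the paragraph does not justify 30 per group at 80% power for the primary outcome.

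**What to change.** Keep 60 patients and rewrite the paragraph:

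1. Relabel 0.52 and 0.56 (correcting 0.55) as raw differences in item means, and drop the word moderate.
2. Report standardised effects from one consistent choice of SDs. Control and experimental SDs of 0.79/0.75 and 0.88/0.75 give 0.68 and 0.69. If the observed SDs are used in both arms, the values from the rounded differences are 0.66 and 0.64. Do not mix the two sets.
3. State whether the test is one- or two-sided.
4. Replace the 80% claim for social-cognitive with the power that 30 per group gives. With SDs 0.79/0.75 this is about 74% unadjusted and two-sided. Beside it, give the power under the planned baseline-adjusted analysis for a stated range of baseline correlation, for example 78% at 0.3 and 86% at 0.5 (both correlations assumed).

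The cost is one rewritten paragraph and a less favourable stated power. No extra patients are needed.
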